**Fig. 1 Fig1:**
[figure not shown]
Locations and catchment areas of the two registry offices of the Cancer Registry in Mecklenburg-Western Pomerania by postal code areas, map adapted from the registry’s webpage (The Cancer Registry of Mecklenburg-Western Pomerania 2024)

### Design of the target trial and the emulated trial

To answer our research question, this study will follow a two-step implementation process. First, we designed a hypothetical target trial protocol to compare the effect of the surgical treatment modalities on 5 year OS in patients with stages I–III colon cancer. Next, we will use real-world data from the Cancer Registry in Mecklenburg-Western Pomerania to explicitly and validly emulate the prespecified target trial. Table 1 summarizes the components of the specified hypothetical target trial protocol and the corresponding planned emulated trial using population-based cancer registry data. Hernán and Robins outlined seven key components that are essential for specifying target trial emulation studies (Hernan and Robins 2016). It is, however, possible to add other components such as the research question and the aim of the study, as Martinuka and colleagues implemented in their COVID-19 study (Martinuka et al. 2023).

**Table 1 Tab1:** Components of the hypothetical target trial and the emulated trial

Study component	Target trial	Emulated trial
Research Question	Does laparoscopic colectomy improve the 5 year overall survival rate compared to open colectomy in patients with stage I–III colon cancer?	Same as target trial
Aim	Compare the 5 year OS of patients with stage I–III colon cancer treated by laparoscopic colectomy or open colectomy.	Same as target trial
Design	Phase III, multicenter, open-label, two-parallel-arms RCT	–
Eligibility	Patients with solitary, primary stages I–III colon cancer aged ≥ 18 years at diagnosis, with performance score (Eastern Cooperative Oncology Group, ECOG ≤ 2 or Karnofsky score ≥ 50%), and Charlson comorbidity index (CCI ≤ 2).	Patients with solitary, primary stages I–III colon cancer aged ≥ 18 years at diagnosis, with performance score ECOG ≤ 2 or Karnofsky score ≥ 50%, and laparoscopic or open colectomy within 3 months (90 days) after diagnosis. CCI is not documented by Mecklenburg-Western Pomerania Cancer (MV) Registry center.
Exclusions	Body mass index (BMI) > 35 Kg/m², advanced local disease (T4), adenocarcinomas of the transverse colon and rectum (including that of appendix, hepatic flexure, splenic flexure, overlapping sites and unspecified cancer of the colon), multiple primary colon tumors, prior history of cancer in the past 5 years. However, patients with non-melanoma skin cancer (NMSC) as well as in situ tumors (ICD-10 codes D00-D09) and benign tumors (ICD-10^a^ codes D10-D36) will not be excluded. The following patients will also be excluded: patients who underwent emergency colectomy, patients with gastrointestinal stromal tumor (GIST), neuroendocrine cancers, sarcoma cases, or patients with previous abdominal surgery. Additional excluded cases include robotic colectomies (OPS = 5–987).	Advanced local disease (T4), patients diagnosed with subtypes of colon cancer located on the appendix (C18.1), hepatic flexure (C18.3), transverse colon (C18.4), splenic flexure (C18.5), or overlapping sites of the colon (C18.8), and all unspecified sites (C18.9) – as well as cancer of the rectosigmoid junction (C19) will be excluded. Patients with prior history of cancer in the past 5 years (except NMSC, in situ tumors (ICD-10 codes D00-D09) and benign tumors (ICD-10 codes D10-D36)) will be excluded. In addition, patients with an additional GIST diagnosis, neuroendocrine cancers, sarcoma cases, patients with previous abdominal surgery for malignant indications as well as patients treated with emergency or robotic colectomy (OPS = 5–987) will also be excluded. Since data on BMI, previous surgery for non-malignant indications and CCI are not available in MV cancer registry, we will not use these covariates as exclusion criteria.
Treatment strategies	1. Laparoscopic colectomy 2. Open colectomy	Same as target trial
Grace-period for treatment implementation	–	The first three months after confirmed stages I–III colon cancer diagnosis.
Treatment assignment	Randomization, at baseline	The patient’s assignment to one of the two treatment strategies will be non-random. But randomness will be emulated by cloning patients in both arms.
Outcome	Death from all causes over a follow-up period of 60 months from baseline (start of follow-up)	Same as target trial (5 year OS)
Type of outcome	Time-to-event data	Same as target trial
Follow-up	Follow up begins at diagnosis and the random allocation of patients to either treatment arms and then scheduled follow-up information according to German S3- guideline for colorectal cancer (German Guideline Program in Oncology 2019).	Patients will be followed from time-zero (date of diagnosis) until death from any cause, last date of information or administrative censor date (31.12.2023), whichever will come first.
Censoring	Loss to follow-up, administrative censor date (31.12.2023).	Same as target trial
Causal contrast	Intention-to-treat effect, per-protocol	Observational analogue of the per-protocol effect
Effect measure	Hazard ratio (HR), mean survival time difference	Same as target trial
Analysis plan	Multivariable Cox regression, absolute risk difference and restricted mean survival time (RMST)	Inverse-probability weighted Royston- Parmar parametric survival model. Further to the HR, absolute risk-difference, RMST difference will be calculated.
Covariate adjustments	ϖ Socio-economic characteristics: Age at colon cancer diagnosis (in years) and sex. ϖ Clinical characteristics: UICC^b^ stage (I, II or III), treating institutions, tumor laterality (left or right), treatment period (2008–2009, 2010–2014, 2015–2018), performance score (ECOG = 0, 1, or 2), hospital classification (certified colon center or not), local residual tumor margin status (yes, no, or not assessable), grade (low, intermediate or high), and number of harvested lymph nodes (< 21 or ≥ 21).	ϖ Socio-economic characteristics: same as target trial. ϖ Clinical characteristics: same as target trial.
Sensitivity analysis	Excluding cases with missing values (complete case analysis, CCA)	Sensitivity analyses: - 1) Repeat the same analysis on patients with complete case data - 2) Including all advanced local disease (stage T4N0-2M0) cases - 3) Quantitative bias analysis using the E-value method to evaluate the effect of potential residual confounders (BMI, comorbidity, previous abdominal surgery for non-malignant indications)
Comparator analysis		Comparator analyses: - Comparator 1) DAGs-guided naïve analysis of using fully adjusted cox proportional hazards model - Comparator 2) An Inverse-probability-weighted regression-adjustment (Doubly robust) analysis

^a^ ICD-10 = The International Classification of Diseases, 10th Revision

^b^ UICC = Union for International Cancer Control

The target trial design would include all adult patients (18 years or older) with solitary colon cancer, stages I–III. In addition, patients with a good performance status (Eastern Cooperative Oncology Group, ECOG ≤ 2 or Karnofsky performance status score ≥ 50%), and Charlson comorbidity index (CCI score ≤ 2) will be included. The target trial would exclude patients with an age less than 18 years, a body mass index (BMI) greater than 35 kg/m², prior abdominal surgery for non-malignant indications, treatment after 3 months of diagnosis, cancer of the transverse colon and rectum (within 15 cm of the anal verge on rigid sigmoidoscopy), cancer of the hepatic flexure of the colon, splenic flexure of the colon, overlapping sites of the colon, appendix and unspecified adenocarcinomas of the colon as identified by ICD-10 topographical subcodes, advanced local disease (T4) or adjacent organ invasion, multiple primary colon tumors, prior history of cancer except non-melanoma skin cancer and benign or in situ tumors. Patients with missing ICD-10 topographical subcodes of colon adenocarcinomas, who had an additional diagnosis of gastrointestinal stromal tumor (GIST), neuroendocrine cancers, or sarcomas, and patients who underwent emergency colectomy or robotic colectomy (OPS = 5–987) will also be excluded. In general, our inclusion and exclusion criteria are largely consistent with those of previous RCTs (Bagshaw et al. 2012; Deijen et al. 2017; Lacy et al. 2008). The emulated trial will use almost the same inclusion and exclusion criteria listed in the target trial design, with the exception of BMI, previous history of surgery for non-malignant indications, and CCI, which are not recorded in the cancer registry (see Table1).

The target trial would use either open or laparoscopic surgery as its treatment strategies. The treatments we aspire to evaluate are similar to those of the target trial, but only open and laparoscopic surgeries performed within three months after first colon cancer diagnosis are defined as our treatment strategies. From the perspective of clinical practice, patients are unlikely to undergo surgery on the same day that their colon cancer diagnosis is confirmed. In this context, it is important to determine the time period in which treatment strategies can be implemented to reflect local clinical practice and minimize patient heterogeneity (Hernan and Robins 2017). Since the initiation of surgery after diagnosis requires time, mainly related to diagnostic workup, a time frame (grace-period) must be taken into account in which most colon cancer patients are likely to undergo surgery.

Eligible participants will be randomly assigned to one of the two treatment modalities stratified by tumor stage and hospital and will be unblinded about the treatment they will be receiving in the target trial. In an open-label, multi-institutional, randomized, two-arm phase III trial, Kitano and colleagues randomly assigned patients with stage II–III colon cancer to either laparoscopic or open colectomy one day before surgery (Kitano et al. 2017). Similar to this RCT, our target trial study would randomize the patients one day before the day of surgery, but with a three-months grace-period to allow for successful implementation of the surgical treatment modalities. The incorporation of a grace-period into a pragmatic trial design prevents ill-defined interventions and improves the use of observational data by expanding the pool of patients who can be included in emulated studies while helping capture real-world clinical practice (Hernan et al. 2016; Hernan and Robins 2016). Accordingly, in our emulated study, patients will be classified into either the laparoscopic colectomy group or the open colectomy group for the treatment of colon cancer within the specified grace-period according to the surgical procedures performed as documented in the patients’ cancer registry records. In contrast to the randomized allocation of patients described in the hypothetical RCT mentioned above, the patients in the emulated trial will not be assigned randomly to one of the treatment modalities. Nevertheless, randomness will be emulated by controlling confounders at baseline using inverse-probability weighting methods and/or via cloning of patients in both arms (Hernan and Robins 2016).

Patients will be followed up from the date of assignment to either treatment modality until death from any cause (the outcome of interest), the last date of follow-up, or the administrative censor date (31.12.2023), whichever occurs first. This administrative censor date is chosen to ensure that patients are observed for at least five years. Patient follow-up will be made in accordance with the recommendation of the German S3- guideline for colorectal cancer (German 2019). In the emulated study, we will start following the patients at time-zero, which is defined as the time point at which the eligibility criteria will be met. The initiation of treatment will have to occur within the first three months after the diagnosis of colon cancer (defined grace-period). Follow-up will end on the date of death, last date of follow-up, or 60 months after time-zero, or the administrative censor date Dec. 31, 2023, whichever will occur first. The main outcome will be 5-year OS, which refers to the duration from time-zero until death from any cause. The estimated hazard ratio will be complemented by the mean survival difference (at 1, 3, and 5 years) between the patients treated with laparoscopic and open surgery, respectively. Since our study covers a long period of time (2008 to 2018), treatment period-specific analyses will be performed to mitigate potential bias that may be induced by changes in clinical knowledge and practice over time (Hou et al. 2022).

#### Statistical analysis

Patient characteristics will be summarized using frequencies and percentages for categorical variables, whereas means and standard deviations or medians and interquartile ranges will be used for continuous variables, depending on their distributions.

We will use the clone-censor-weight design to emulate the hypothetical target trial (Hernan and Robins 2016). Since each patient will be eligible for one of the two surgical treatment modalities during the three-month grace-period, we will first clone (copy) each patient record, and each clone will then be allowed to enter both treatment arms for the duration of the grace-period regardless of the surgical modality they will actually receive later. This will emulate randomization in the specified target trial and addresses the issue of confounding at baseline, as both treatment arms are identical in terms of baseline patient characteristics. Cloning also offers the opportunity for even distribution of survival times (before surgery, for the entire grace-period or any early deaths that may occur before treatment) between the two surgical treatment modalities, allowing us to circumvent the problem of immortal time bias (Hernan and Robins 2016). In the next step, we will censor clones over time if non-compliance with the initially assigned treatment strategy is detected from that timepoint onward. This implies that we will censor clones assigned to laparoscopic colectomy (including converted colectomy) but whose records indicate that they underwent open colectomy within the grace-period, or vice versa. The censoring times will be defined corresponding to the time of each censoring event and will be incorporated into the weighting model described below. Figure2 provides all possible treatment paths and the respective censoring mechanism of the trial emulation for both treatment and outcome models.

**Fig. 2 Fig2:**
[figure not shown]
Definition of outcome and survival times for each patient in each emulation arm

The informative censoring (and hence associated selection bias) induced by the implementation of artificial censoring will be adjusted via inverse-probability censoring weighting (IPCW). This will reflect the likelihood of being compliant (uncensored) with the assigned treatment strategy given the confounding factors. However, prior to cloning, an inverse-probability of treatment weighting (IPTW) on the uncloned (original) population will be estimated with the aim of assigning larger weights to patients who will be less likely to undergo laparoscopic colectomy, given the individual constellation of confounding factors. These weights (IPTW and IPCW) will be estimated by running separate models using a logit function and later combined by multiplying both weights. This single combined weight will later allow us to determine an unbiased causal effect of laparoscopic versus open surgical treatment. We will then use absolute standardized differences within ≤ 10% as an indicator of adequate balance of the covariates (confounders) between the two treatment arms. If there will be evidence of imbalance, the weights at the 1st and 99th percentiles will be trimmed to reduce the effect of extreme weights. This will be achieved by replacing all weight values that are below the 1st percentile with the 1st percentile value and by replacing all weight values above the 99th percentile with the 99th percentile value.

Intention-to-treat and per-protocol effects are used as causal contrasts for the target trial design. The intention-to-treat effect refers to the comparative effect of laparoscopic versus open colectomy, independent of subsequent non-compliance that may occur later after time-zero due to conversion from laparoscopic to open colectomy. The per-protocol effect, on the other hand, refers to the comparative effect of exclusive receipt of laparoscopic versus open colectomy. In contrast, the observational-analogue of the intention-to-treat effect will not be estimable in the emulated study because our emulation process will be implementing a grace-period with the cloning-censoring-weighing method. This means that every eligible patient will be assigned to both treatment arms during this period until they will be censored if their treatment modality will deviate from the modality to which they were initially classified. Therefore, our causal contrast of interest in the emulated study will only be the observational-analogue of the per-protocol effect of laparoscopic versus open colectomy performed in the first three months after colon cancer diagnosis.

Finally, we will use an inverse-probability weighted Royston-Parmar parametric survival model (RPpsm) to estimate an unbiased causal effect of laparoscopic versus open surgical treatment on OS via hazard ratio. If incorporating the final weight (derived from IPTW and IPCW) into the RPpsm will not be achieved, we will alternatively use weighted pooled logistic regression to model the outcome. When the event of interest (death from any cause) occurs, that event is considered to be an event solely in the patients’ originally planned treatment arm, in which each patient is initially consistent and remains uncensored at the point in time when the event occurs. On the other hand, the cloned records will be censored at that exact time the event occurs, which is accomplished by censoring indicators. Using weighted RPpsm postestimation tools, OS will be estimated using differences in absolute risk and restricted median survival (RMST) at 1-, 3-, and 5-years and up to 1-, 3-, and 5-years, respectively. To account for the weighting to be applied, point estimates will be accompanied by 95% confidence intervals via non-parametric bootstrapping with 500 replicates. A weighted Kaplan-Meier method will be used to compare time-to-event curves over a 60-months period according to surgical treatment modality. We will compare our results with estimates from the literature. We make use of the CERBOT (Comparative Effectiveness Research Based on Observational Data to Emulate a Target Trial) tool (see Additional file 1) in our emulation process (Zhang et al. 2024).

It is crucial to handle missing data properly to obtain more powerful models resulting in better estimates (Mbona et al. 2023). We will use multiple imputation via the chained equations method to impute missing values in covariates, assuming that observed missing values are missing at random (White and Royston 2009). In the literature, this method is also referred to as “multivariate imputation with sequential regression” and “imputation using fully conditional specifications” (Raghunathan et al. 2001; van Buuren et al. 1999). All variables of the analysis dataset, including the outcome variable, will be used for the imputation model and ten datasets (m = 10) will be imputed.

In the web-based DAGitty environment (https://www.dagitty.net/), we will utilize directed acyclic graphs (DAGs) to determine the minimum necessary adjustment sets of confounders to control for within the comparative multivariable model. This approach mitigates the risk of bias that may arise from conditioning on intermediate covariates or colliders and mediators (Textor et al. 2011; Tonnies et al. 2022). The causal diagram for the comparative multivariable Cox model is complemented by a literature review and discussion to identify confounders, colliders, mediators and prognostic factors (Austin and Stuart 2015; Lederer et al. 2019). By adjusting the minimum sufficient adjustment sets of confounders in our comparative model, we will be able to block any backdoor bias paths (remove relevant confounding) when estimating the total causal effect of surgical treatment modality on all-cause mortality.

We will consider the following baseline characteristics (measured before or at time-zero) as potential confounders: Age at colon cancer diagnosis, sex, year of surgical treatment (classified according to the implementation and update series of the German S3- guideline for colorectal cancer (German Guideline Program in Oncology 2019) as 2008–2009 [pre-implementation], 2010–2014 [first update], or 2015–2018 [second update]), tumor laterality (right-sided [caecum and ascending colon] tumor or left-sided [descending and sigmoid colon] tumor), hospital type (classified as either a registered colorectal cancer center or other group), performance status (ECOG ≤ 2 or Karnofsky performance status score ≥ 50%), and histologic grade (low, intermediate or high), UICC stage (I, II or III), and local tumor size (T-stage). In addition, we will adjust the following two variables that serve as quality indicators of performed surgical procedure: minimum number of harvested lymph nodes (classified as < 21 or ≥ 21) (Choi et al. 2010), and local residual tumor status within 3 months of diagnosis (no (R0), yes (R1 + R2), not assessable or missing). We will also extract the following dates accurate to the month (date of birth, diagnosis, surgery, death, neo/adjuvant therapy initiation, and conversion to open surgery) and other covariates (project specific pseudonym, tumor IDs, cause of death).

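### The treatment weight is described only by the chance of laparoscopy, which is reversed for open-surgery patients, and its product with the censoring weight misses the eligible cohort on either reading

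*Protocol article*

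**What the plan says.** All of this is in the protocol article, Methods, Statistical analysis, unless noted.

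- Cloning is said to settle baseline confounding; it "addresses the issue of confounding at baseline, as both treatment arms are identical in terms of baseline patient characteristics".
- Artificial censoring is handled by an IPCW: "This will reflect the likelihood of being compliant (uncensored) with the assigned treatment strategy given the confounding factors".
- A second weight is added: "prior to cloning, an inverse-probability of treatment weighting (IPTW) on the uncloned (original) population will be estimated". The stated purpose of this second weight is put as follows: "with the aim of assigning larger weights to patients who will be less likely to undergo laparoscopic colectomy". No formula is given, and the operation actually received is not mentioned.
- The two weights "will be estimated by running separate models using a logit function and later combined by multiplying both weights". The product is carried into the weighted survival model, from which the hazard ratio, absolute risks and RMST are derived.
- Balance is judged between the arms: "We will then use absolute standardized differences within ≤ 10% as an indicator of adequate balance of the covariates (confounders". Trimming at the 1st and 99th percentiles is the only stated response to imbalance.
- The target is the "observational-analogue of the per-protocol effect of laparoscopic versus open colectomy performed in the first three months after colon cancer diagnosis". No population other than the eligible patients is named.
- The section on the design of the target and emulated trials is looser about the mechanism: "randomness will be emulated by controlling confounders at baseline using inverse-probability weighting methods and/or via cloning of patients in both arms".

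**The concern.** A treatment weight inverts the probability of the treatment received. With e = P(laparoscopy | covariates), it is 1/e for a laparoscopic patient and 1/(1−e) for an open patient. An open patient who was unlikely to get laparoscopy had the expected operation and should get a small weight. The sentence in the article says the opposite for that patient.

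The weight does not stand alone. After cloning and censoring, the IPCW already corrects for who ends up in which arm. Any further factor that depends on e changes the population that the weighted arms represent. The article says that the combined weight will give an unbiased causal effect, so the question is what that product delivers under each way an analyst could code the sentence. At stake are the survival and RMST reported by arm, their differences if the effect is not uniform and, on one reading, the between-arm comparison itself.

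**Working it through.** The article states no weight formula, propensity, event rate or sample size, so there is no figure of the plan to reproduce. The check is exact arithmetic on a two-stratum population.

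**Assumed inputs.** One binary confounder X, with half the cohort in each stratum. e = 0.5 in the low-risk stratum (X=0) and 0.2 in the high-risk stratum (X=1). Five-year death risk is 0.20 and 0.50, the same for both operations (null effect). True mortality in the eligible cohort is 0.5×0.20 + 0.5×0.50 = 0.350.

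**Censoring weight.** Table 1 limits the emulated trial to patients with laparoscopic or open colectomy within 90 days. Each patient therefore ends up compliant with exactly one arm. Treating this as one decision with no other censoring, the IPCW is 1/e in the laparoscopic arm and 1/(1−e) in the open arm.

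**Uncensored patients, as fractions of the cohort.** Laparoscopic: 0.25 (X=0) and 0.10 (X=1). Open: 0.25 and 0.40.

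**Treatment weight as worded (1/e for all) times IPCW.**
- Laparoscopic, 1/e²: 0.25/0.25 = 1.0 and 0.10/0.04 = 2.5. High-risk share 2.5/3.5 = 0.714.
- Open, 1/[e(1−e)]: 0.25/0.25 = 1.0 and 0.40/0.16 = 2.5. High-risk share 0.714.

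**Standard treatment weight times IPCW.**
- Laparoscopic, 1/e²: 0.714 as above.
- Open, 1/(1−e)²: 0.25/0.25 = 1.0 and 0.40/0.64 = 0.625. High-risk share 0.625/1.625 = 0.385.

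The eligible cohort has a high-risk share of 0.500. SMD is the standardised difference and RD the risk difference, both laparoscopic minus open, under the null effect.

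| Weight | Share, lap | Share, open | SMD | RD |
|---|---|---|---|---|
| None | 0.286 | 0.615 | −0.70 | −0.099 |
| IPCW alone | 0.500 | 0.500 | 0 | 0 |
| As worded, alone | 0.500 | 0.800 | −0.66 | −0.090 |
| As worded × IPCW | 0.714 | 0.714 | 0 | 0 |
| Standard × IPCW | 0.714 | 0.385 | +0.70 | +0.099 |

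**As worded × IPCW, absolute risk.** Each arm shows 0.20 + 0.30×0.714 = 0.414 instead of 0.350, which is 6.4 points too high. The between-arm SMD is 0, so the planned check passes.

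**As worded × IPCW, effect that varies.** If laparoscopy lowers the risk only in the high-risk stratum, from 0.50 to 0.40, the true RD is 0.5×(−0.10) = −0.050. The tilted arms give 0.714×(−0.10) = −0.071.

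**Other assumed propensities.**

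| e (X=0 / X=1) | As worded × IPCW: share in both arms | Mortality (true 0.350) | RD when true is −0.050 | Standard × IPCW: shares lap / open | False RD under null |
|---|---|---|---|---|---|
| 0.4 / 0.1 | 0.800 | 0.440 | −0.080 | 0.800 / 0.400 | +0.120 |
| 0.6 / 0.3 | 0.667 | 0.400 | −0.067 | 0.667 / 0.364 | +0.091 |
| 0.3 / 0.2 | 0.600 | 0.380 | −0.060 | 0.600 / 0.467 | +0.040 |

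**Trimming.** With the standard weight the balance check would flag the imbalance (SMD +0.27 to +0.89 over these cases). In the base case every stratum-by-arm cell holds at least 10% of the cohort, so trimming at the 1st and 99th percentiles changes nothing.

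**The case against.** The strongest reply is that the article gives an aim, not a formula. It names a standard method fitted with a logit model, and that method by definition uses the treatment received. The sentence is right for laparoscopic patients, and loose prose in a condensed article is at least as likely as a wrong formula. An exact formula may also sit in an analysis plan that is not shown. This stands as far as it goes: the lack of a formula is no finding, and a reader who infers that the weight is defined regardless of the operation received is reading that into silence. It does not rescue the plan, because the multiplication is stated outright and the standard weight is the reading under which the product unbalances the arms. Weighting to the open-surgery population would also fit the words, but it is nowhere declared.

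Two stronger readings are tempting and not supported.

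- A reader might infer that the weight leaves confounding worse than no weighting. That concerns the weight used alone, which the and/or remark in the design section might seem to allow, but the Statistical analysis section commits to cloning, censoring and the product. Nor is it generally true of the weight alone: the open arm moves away from the cohort (0.615 to 0.800), yet the gap between arms narrows from 0.329 to 0.300. The 10% check would also flag it.
- A reader might infer that the wording as it stands biases the comparison under no effect. It does not: the product then leaves the risk difference at zero, and the excess mortality is common to both arms.

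**Conclusion.** The point holds in a limited form. The stated direction of the treatment weight is reversed for open-surgery patients, and the weight feeds the primary model. On neither main reading does the product represent the eligible cohort.

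- **Coded as worded:** the arms match each other but not the cohort. In the illustration, 5-year mortality is 3 to 9 points too high in both arms, and a true difference of −5.0 points reads −6.0 to −8.0 when the effect varies between patients. RMST was not computed, but it is exposed to the same tilt. The planned balance check does not reveal this.
- **Coded as a standard treatment weight:** treatment choice is weighted for twice. The false difference under no effect is 4 to 12 points against laparoscopy. The balance check would flag it, but the plan has no effective remedy.

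All sizes rest on assumed propensities, risks and a single binary confounder. They show direction and plausible scale, and are not estimates for this registry. The directions follow from the form of the weights, given that laparoscopy is less likely in higher-risk patients.

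**What to change.** 1. Delete the sentence on the treatment weight and the multiplication, and weight the cloned data by the arm-specific IPCW alone. In the illustration this gives a high-risk share of 0.500 in both arms and a null difference of zero. Amend the later reference to a final weight built from both components, and the and/or remark in the design section, to match.
2. If a treatment weight is wanted, confine it to an analysis of the uncloned cohort: 1/P(lap|X) for patients operated laparoscopically and 1/(1−P(lap|X)) for patients operated openly. Never multiply it by the treatment-compliance IPCW. Correcting only the direction while keeping the product is not a repair, because it leads to the unbalanced case above.
3. Name the eligible cohort as the target population.
4. Compare each arm's weighted covariate means with the unweighted eligible cohort as well as with the other arm. That comparison would show 0.714 against 0.500.

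The cost is a few sentences and one extra column in the balance table, with one model fewer in the primary analysis. No data or design change is needed.
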